### Outcome Measures

The primary outcomes of this study are about the effects of nicotine on achromatic contrast sensitivity at the various spatial frequencies (Study 1) and on chromatic contrast discrimination using the Trivector threshold values and the various elliptical parameters like angle of the major axis, major axis length, axis ratio, and area (Study 2). For Study 1, the higher the curve, the better the discrimination ability. For Study 2, the area of the ellipse is a general index of chromatic discrimination. That is, the smaller the ellipse, the better the discrimination ability. Provided that there is a statistically significant main effect or interaction, results will be related to the statistical analysis: an improvement of 10% will be considered as meaningful difference for each spatial frequency (Study 1) and for each parameter of the CCT (Study 2). The primary outcome will be assessed after the three sessions are completed. As previously noted, we did not observe learning or practical effects when using Metropsis software (Fernandes et al., 2019a) and the CCT (Fernandes et al., 2020). The secondary outcomes are related to demographic data (effects of age, years of education, height, and weight), BMI, and gender effects. Serum cotinine levels (ng/ml) after each session (placebo, 2 mg, and 4 mg of nicotine gum) will be used as predictors of response (for each visual test) in a multivariate regression analysis. Data will be double-checked and stored at an open access repository (figShare; available upon request).

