#### Study 1—Contrast Sensitivity Function

The Metropsis software (Cambridge Research Systems Ltd., Rochester, United Kingdom) will determine contrast sensitivity. The stimuli for the CSF will be linear, vertically oriented, sine-wave gratings with spatial frequencies ranging from 0.2 to 20.0 cycles per degree (cpd). We will constantly check the outcomes, using the experimenter’s monitor, to observe any floor or ceiling effects of the spatial frequencies. The stimuli consist of equiluminant gratings with dimensions of 5° of a visual angle and will be presented on the monitor at 2.5° spatial offset from the central cross-shaped fixation point (Fernandes et al., 2019b).

Small sample sizes are common in perception research owing to the repeated measures design. However, some researchers still debate whether small sample sizes are reliable and generalizable. The Metropsis software represents a reliable tool to investigate contrast sensitivity and does not require multiple applications and does not suffer variation over time within-subjects. This tool can be used in small sample sizes and still provide reliable data as we previously observed (Fernandes et al., 2019a). Psychometric function of the Metropsis software (e.g., employing a rigorous criterion of almost 80% correct responses for each spatial frequencies) is one of its main advantages. Measures of reproducibility were undertaken (Fernandes et al., 2019a), and values above or below the reported means for each spatial frequency used will be considered as statistically significant differences.

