#### Study 1—Contrast Sensitivity Function

For the contrast sensitivity analysis, we will use a multivariate analysis of variance (MANOVA), with eight dependent variables (thresholds of each spatial frequency; continuous variables) and one independent, within-subject variable (condition ∼ three levels). *Post hoc* testing will be conducted using discriminant analysis.

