#### Study 2—Cambridge Colour Test

For the Trivector subtest of the CCT, we will use a one-way MANOVA, with three dependent variables (thresholds for protan, deutan, and tritan; continuous variables), and one independent, within-subject variable (condition ∼ three levels). For the Ellipse subtest, we will conduct a separate MANOVA for Ellipse 1 with two dependent variables (angle and area; continuous variables) and one independent, within-subject variable (condition ∼ three dosage). A moderation or mediation analysis (using 5,000 bootstrapping resamples) will be conducted to determine whether the area, length, angle, or ratio is a better predictor of any results of the CCT.

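### Once an omnibus test is significant, the 10% rule calls single spatial frequencies and colour parameters meaningful with no test or interval for that parameter

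*Protocol article*

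**What the plan says.** Outcome Measures sets a gate, "Provided that there is a statistically significant main effect or interaction, results will be related to the statistical analysis", and then the label: "an improvement of 10% will be considered as meaningful difference for each spatial frequency (Study 1", with the same threshold for each CCT parameter in Study 2. These are the primary outcomes of both studies.

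The tests that could open the gate are under Statistical Analysis:

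- **Study 1:** one MANOVA "with eight dependent variables (thresholds of each spatial frequency; continuous variables) and one independent, within-subject variable" at three levels (placebo, 2 mg, 4 mg). As the follow-up step, "testing will be conducted using discriminant analysis".
- **Study 2, Trivector:** a one-way MANOVA "with three dependent variables (thresholds for protan, deutan, and tritan; continuous variables".
- **Study 2, Ellipse:** a separate MANOVA on angle and area only. No follow-up test of condition is named for either Study 2 analysis.

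Outcome Measures lists four ellipse parameters as primary: angle, major axis length, axis ratio and area.

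A second rule for single frequencies stands under Material and Stimuli, Study 1. It refers to an earlier reproducibility study and says that "values above or below the reported means for each spatial frequency used will be considered as statistically significant differences".

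**The concern.** An omnibus test answers whether anything differs between the conditions. It does not say which frequency or parameter differs. The 10% label is applied at exactly that finer level, and as worded it needs only a point estimate. If one frequency truly responds and makes the MANOVA significant, the other seven, at two doses each, can be labelled on noise.

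This matters because the Introduction and the Study 1 aims tie low, middle and high spatial frequencies to the magnocellular and parvocellular pathways. A false label at one frequency therefore becomes a false statement about a pathway.

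Three lesser defects belong with it. Major axis length and axis ratio can earn the label without entering any MANOVA of condition. A percentage improvement is undefined for the ellipse angle, which has an arbitrary zero and no better direction. The rule also names improvement only, although the Introduction allows that nicotine or another smoke component could impair photopic vision.

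**Working it through.** The plan gives no error rate for this rule, so there is no figure of its own to reproduce.

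**Inputs from the protocol:** 42 completers per study and two-sided alpha 0.01 (Sample Size); 8 frequencies and 3 conditions (Statistical Analysis, Study 1); the 10% threshold (Outcome Measures).

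**Inputs assumed:**
- SD of the within-person log10 dose-minus-placebo difference: 0.10 to 0.25.
- Correlation between frequencies: 0.2 to 0.5.
- Correlation between the two dose contrasts: 0.5, through the shared placebo.
- One frequency affected at both doses, by 15% or 30%.
- The omnibus test taken as a Hotelling T² test on the 16 dose-to-placebo differences, at 0.01.

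**Step 1, one unaffected contrast.** The threshold is log10(1.1) = 0.0414. SE = SD/√42 and z = 0.0414/SE. The chance that an unaffected contrast shows a 10% gain is 1 − Φ(z). Example for SD 0.15: SE = 0.15/6.481 = 0.0231, z = 1.79, probability 3.7%. A gain of exactly 10% then has an unadjusted two-sided p of about 0.07, so the label can go to a difference that its own unadjusted 95% interval does not separate from zero.

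**Step 2, a family of 7 × 2 = 14 unaffected contrasts.** Multivariate-normal simulation, first ignoring the gate and then only among draws in which the gate opened:

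| SD | z | One contrast | Any of 14, gate ignored | Any of 14, given open gate |
|---|---|---|---|---|
| 0.10 | 2.68 | 0.4% | 4–5% | 3–8% |
| 0.15 | 1.79 | 3.7% | 26–34% | 27–48% |
| 0.20 | 1.34 | 9.0% | 47–60% | 51–68% |
| 0.25 | 1.07 | 14.2% | 62–75% | 66–84% |

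The last column carries a few points of simulation error, because the gate rarely opens at high SD. With 100,000 draws, the top of the 0.20 row came out at about 73%.

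**Step 3, joint chance that the gate opens and a false label follows.** For a true 15% gain the gate opens in about 39–68% of trials at SD 0.10 but only 3–5% at SD 0.25, and the joint chance is about 3–8% across all SDs. For a true 30% gain the joint chance is about 3–5% (SD 0.10), 24–25% (0.15), 21–29% (0.20) and 13–21% (0.25), so about 3–29% overall.

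**Step 4, cross-check on another scale.** An SD of 0.15 for the log10 difference corresponds to a within-person CV of about 25% (0.15 × 2.303/√2 = 0.244 on the natural-log scale). A separate simulation in CV terms, conditional on a significant omnibus test at 0.01, gave 2% at CV 15%, 36% at CV 25% and 74% at CV 40%. When a Bonferroni paired test at 0.05/16 also had to be passed, these fell to 1.4%, 3.2% and 4.6%.

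**Step 5, Study 2.** There are 3 Trivector thresholds and 4 ellipse parameters, so 6 × 2 = 12 contrasts if one parameter is affected. Ignoring the gate, and treating all parameters as ratios, the chance of at least one false label at CV 25% is about 25–35% (correlation 0.5 to 0).

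**Step 6, the other provisions.** Discriminant analysis finds the weighted combination of frequencies that best separates the conditions. It neither tests nor bounds the change at one frequency. The sentence about earlier means uses an outside reference instead of placebo and no test: almost every observed value lies above or below a fixed mean.

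**The case against.** The best defence is that 10% is a threshold of relevance added to significance, not a replacement for it. Outcome Measures does make the label conditional on significance, and that condition has real effect: where noise is large enough to give the highest figures, the gate seldom opens. A reader might infer that the plan has no control over false frequency-specific claims, or might read 4–75% as the plain chance of one. The documents support neither. Those figures ignore the gate, and the joint figures are much lower. What remains is that the significance belongs to the whole set of frequencies while the label belongs to one of them.

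Second, the variability is assumed. Material and Stimuli describes the contrast test as reliable and stable within a person, which points to the low end, where the risk is only a few per cent. One affected frequency out of eight is also an unfavourable case: the Introduction suggests a stronger effect at high frequencies in general, which would leave fewer unaffected ones. Both points stand. But the rule's error rate then depends on noise that the protocol does not state.

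Third, contrasts and multiplicity adjustment are often left to an analysis plan that is not shown here. That would excuse silence. The article is not silent: it states a decision rule for the primary outcomes.

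Fourth, naming improvement only matches the directional hypothesis, and a MANOVA is not directional. One might infer that impairment would go unseen; it could still make the omnibus test significant. The rule simply gives it no label. The intent of the sentence on earlier means is also unclear without the cited study, so it should not be read as the planned primary test. As worded, it is still wrong.

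**Conclusion.** The point holds in this form: the gate limits how often false labels arise but does not protect unaffected frequencies or parameters once another one opens it, and no other step in the plan tests them singly. Given an open gate, the risk of at least one false label in Study 1 ranges from a few per cent with precise measurements to well over half with noisy ones. Including the gate, it is about 3–8% for a true 15% gain and 3–29% for a true 30% gain. All of this rests on the assumed SDs and correlations, 42 completers, one affected frequency and a gate at 0.01. In Study 2 the gate is two separate MANOVAs, and two primary ellipse parameters lie outside both. The plan should be changed. This is a flaw in a decision rule, not in the design or the data to be collected.

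**What to change.** - For each spatial frequency and each suitable CCT parameter, report the dose-to-placebo ratio, estimated on the log scale, with a multiplicity-adjusted confidence interval. Holm or simultaneous intervals are examples; other valid adjustments would serve.
- Call a change meaningful only if that interval excludes no change and the estimate is at least 10%. Report changes in either direction.
- Apply this to major axis length and axis ratio too, so that neither is labelled untested.
- Take the ellipse angle out of the percentage rule and report its difference in degrees with an interval.
- Delete the Study 1 sentence on departures from earlier means, or replace it with the within-trial comparison against placebo.

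The cost is analysis wording and somewhat fewer parameters declared meaningful. No extra participants, visits or measurements are needed.

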### Material and Stimuli

The stimuli will be presented on a gamma-corrected 19-inch LG CRT monitor with 1,024 × 786 resolution and a 100-Hz refresh rate. Stimuli will be generated using a VSG 2/5 video card (Cambridge Research Systems), which will be run on a Precision T3500 computer with a W3530 graphics card. All of the procedures will be performed in a room at 26 ± 1°C. The room lights will be extinguished and so the only light sources will be the computer monitors. The experimenter’s monitor will be positioned so that it is outside of the participant’s field of view. Implementation and calibration procedures (gamma-correction) will be performed with software and hardware provided by the Cambridge Research Systems (a ColCAL MKII photometer). The participant’s head will be stabilized using forehead and chin rests. The participants will be instructed to look at the central cross-shaped fixation point (for Study 1) or the center of the CCT background pattern (for Study 2). They will be informed that once the stimulus is presented, they can move their eyes as required to identify which side has the grating or the gap position on the Landolt ring.

#### Study 1—Contrast Sensitivity Function

The Metropsis software (Cambridge Research Systems Ltd., Rochester, United Kingdom) will determine contrast sensitivity. The stimuli for the CSF will be linear, vertically oriented, sine-wave gratings with spatial frequencies ranging from 0.2 to 20.0 cycles per degree (cpd). We will constantly check the outcomes, using the experimenter’s monitor, to observe any floor or ceiling effects of the spatial frequencies. The stimuli consist of equiluminant gratings with dimensions of 5° of a visual angle and will be presented on the monitor at 2.5° spatial offset from the central cross-shaped fixation point (Fernandes et al., 2019b).

Small sample sizes are common in perception research owing to the repeated measures design. However, some researchers still debate whether small sample sizes are reliable and generalizable. The Metropsis software represents a reliable tool to investigate contrast sensitivity and does not require multiple applications and does not suffer variation over time within-subjects. This tool can be used in small sample sizes and still provide reliable data as we previously observed (Fernandes et al., 2019a). Psychometric function of the Metropsis software (e.g., employing a rigorous criterion of almost 80% correct responses for each spatial frequencies) is one of its main advantages. Measures of reproducibility were undertaken (Fernandes et al., 2019a), and values above or below the reported means for each spatial frequency used will be considered as statistically significant differences.

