### Sample Size

There were no previous reports of sample size estimation from a meta-analysis or equivalent study. Because of the lack of this information, the effect size will be estimated using the minimal meaningful effect size (0.05) (Sullivan and Feinn, 2012) and the power will be used considering a common value in clinical trials (Charan and Biswas, 2013). Considering a two-sided test with an alpha value of 0.01 (or 0.02 for a one-sided test) and a power of 85% (or 0.85), the sample size would require at least 42 individuals to complete the three periods for each study. As this trial is a single group model, with an anticipated 20% attrition rate, our main intention is to enroll 50 individuals for each study (Study 1, *N* = 50; Study 2, *N* = 50). Although our sample size is larger than that of previous studies using these tests (Andrade et al., 2019; Fernandes et al., 2019a,b), it is important to provide an estimation that covers our outcomes (e.g., BMIs and cotinine).

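### Study 1 contains a second, invalid significance rule (any value above or below a historical mean) that conflicts with the planned within-participant MANOVA and its gate

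*Protocol article*

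**What the plan says.** Four places in the protocol article bear on when a Study 1 result counts as significant.

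- **Material and Stimuli, Study 1.** A paragraph defending the reliability of the instrument ends with a reference to earlier work ("Measures of reproducibility were undertaken") and then states that "values above or below the reported means for each spatial frequency used will be considered as statistically significant differences". The earlier means and their spread are not given.
- **Sample Size.** Alpha is 0.01 for a two-sided test, with 0.02 offered for a one-sided test, and power is 85%.
- **Outcome Measures.** A 10% improvement at a spatial frequency counts as meaningful only on a condition: "Provided that there is a statistically significant main effect or interaction".
- **Statistical Analysis, Study 1.** The eight frequency thresholds are the dependent variables of a MANOVA, with condition (three levels) as the within-subject factor. The only follow-up named is that post hoc "testing will be conducted using discriminant analysis".

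The Study 1 aims compare placebo, 2 mg and 4 mg within the same participants.

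**The concern.** The sentence in Material and Stimuli is an affirmative rule about the Study 1 primary outcome. It is not a detail left to an analysis plan that is not shown. It defines significance by position relative to a fixed historical mean. A mean marks the centre of a distribution and sets no limit, so the rule cannot separate a real difference from measurement noise.

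The reference is also external. If these participants differ from the earlier sample in age, setting or equipment, their values would differ from it with no nicotine given, and the rule would call that difference significant.

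The place where the rule applies adds to the problem. The aims and the 10% criterion look for conclusions at low, middle and high frequencies. The MANOVA is an omnibus test, and discriminant analysis describes a weighted combination of frequencies. It does not compare a dose with placebo at each frequency. The quoted sentence is therefore the only significance rule in the article stated frequency by frequency. An analyst who wanted to say which frequencies changed could take it as licence to do so without error control.

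**Working it through.** **Inputs from the article:** eight thresholds, described as continuous, and three conditions (Statistical Analysis, Study 1); alpha 0.01 two-sided, 42 completers and 50 enrolled per study (Sample Size); reference means from an earlier study, values not given.

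**1. The plan's own figures.** The nominal error rate is 0.01 two-sided. A MANOVA omnibus test has no one-sided form, so 0.01 is the figure that applies and the alternative of 0.02 does not. The figure of 42 completers cannot be reproduced without assumptions. The metric of the effect size of 0.05 is not stated. As a paired standardised difference, 0.05 would need ((2.576 + 1.036)/0.05)² ≈ 5,220. As f² in a three-period repeated-measures analysis, it needs 54 at a within-subject correlation of 0.5 and 34 at 0.7. Nothing below depends on this; 42 and 50 serve only as sample sizes for the simulation.

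**2. Literal reading.** For a continuous value X and a fixed reference m, P(X above or below m) = 1 − P(X = m) = 1 − 0 = 1. This holds for single scores and for condition means, and whatever the true mean is. It covers all 8 × 3 = 24 frequency-by-condition cells, of which 8 are placebo cells.

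A simulation of 20,000 trials with no difference from the reference gave:

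| n | Rule as written | One-sample t test at 0.01 |
|---|---|---|
| 42 | 1.000 | 0.0091 |
| 50 | 1.000 | 0.0098 |

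The t test column shows what a rule that uses the spread would do against the same reference.

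**3. Directional reading.** Suppose only values on the improved side count, the true mean equals the reference, and the sampling distribution is symmetric. Then P = 0.5 per frequency. For at least one of eight frequencies in a given condition:

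- perfectly correlated frequencies: 0.5
- independent frequencies: 1 − 0.5⁸ = 1 − 0.0039 = 0.996

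If this sample's true mean differs from the reference, the chance per frequency moves away from 0.5 in a direction that cannot be known in advance.

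**4. The rules side by side.**

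| Section | Reference | Basis for significance | Error rate under no effect |
|---|---|---|---|
| Material and Stimuli, Study 1 | Historical mean | Above or below | 1 (0.5 per frequency if directional) |
| Statistical Analysis, Study 1, with Sample Size | Concurrent conditions, within participant | MANOVA | 0.01 nominal |
| Outcome Measures | Not restated | Significant effect first, then 10% | As for the MANOVA |

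A result can meet the first row and fail the second, and the article does not say which governs.

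**5. What a repair must avoid.** Replacing the sentence with unadjusted dose-versus-placebo tests at 0.01 would also lose error control. If the tests are independent, eight give 1 − 0.99⁸ = 0.077, and sixteen (two doses × eight frequencies) give 1 − 0.99¹⁶ = 0.149.

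**The case against.** The strongest reply is that this is a loose sentence in a paragraph on instrument reliability and was never meant as an analysis rule. The formal test is named under Statistical Analysis, and Outcome Measures makes a significant effect a precondition. The reported means might also be mean test–retest differences, so that the intent was to flag changes larger than measurement noise.

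Much of this stands. A reader might infer that historical means replace placebo as the comparator. The documents do not support that: placebo is a concurrent condition in the aims, in General Study Design and in the MANOVA. A reader might also infer that every Study 1 result will be declared significant. That follows only if this sentence governs, and the MANOVA and the gate point the other way. Nor is the probability of 1 an error rate for the trial's main conclusion. It is a property of the rule read literally, and a placebo value that differs from an old mean is not a false claim about nicotine.

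The noise-band reading does not rescue the text. It would need limits, such as limits of agreement or a repeatability coefficient, and the article gives only means. The intended meaning cannot be settled from the document, and no reading available from the words controls error.

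**Conclusion.** The point holds as a conflict between rules. The sentence sets a second significance criterion for the Study 1 primary outcome that is invalid as written and cannot be squared with the alpha in Sample Size, the gate in Outcome Measures or the within-subject MANOVA.

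Taken literally, its error rate is 100 times the stated alpha (1.00 against 0.01). On the directional reading it is 50 times the alpha at each frequency (0.5 against 0.01). The first figure assumes only that thresholds are continuous, which the article says. The second assumes that the historical mean equals this sample's true mean and that the sampling distribution is symmetric.

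The planned comparison with placebo is intact. The exposure is at the level of individual frequencies, where no other significance rule is stated.

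**What to change.** 1. In Material and Stimuli, Study 1, delete the sentence. Alternatively, recast it as a purely descriptive check of measurement reproducibility, with no reference to significance.
2. In Statistical Analysis, Study 1, state that significance comes only from the within-participant comparison of placebo, 2 mg and 4 mg in the MANOVA, at alpha 0.01.
3. Add that any comparison of a dose with placebo at a single frequency follows only after a significant MANOVA and is adjusted across the eight frequencies and two doses. Holm over the sixteen comparisons would do; its first step uses 0.01/16 = 0.000625. The 10% criterion then stays behind the gate already set in Outcome Measures.

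The cost is one sentence removed or reworded and about two added. No visit, measurement or enrolment target changes. The adjusted per-frequency comparisons will have less power than the omnibus test, and the article should say that the sample size was not derived for them.
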